### Statistical methods

Following PRIMENT SOP, the detail of statistical analyses will be described in a separate statistical analysis plan that will be agreed before final trial data are made available.

#### Statistical methods for primary and secondary outcomes {20a}

Baseline demographic and questionnaire data will be summarised by treatment group using means (with standard deviations), medians (with interquartile ranges), counts, and proportions, as appropriate, to gauge the balance in characteristics between the randomised groups.

#### Primary outcome analysis

Family carer-rated Goal Attainment Scaling (GAS) global mean scores at 12 month follow-up will be summarised for the NIDUS-family and usual care groups using means with standard deviations. The outcome will be compared between the groups using a three level mixed effects model which allows for intervention arm therapist clustering and also includes a random effect for study site. The treatment effect estimate from this model will be the adjusted difference in mean GAS score which will be reported with a 95% confidence interval and *P* value. Analyses will be carried out based on the intention to treat principle, comparing the groups as randomised regardless of adherence to the intervention.

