### Outcomes {12}

All outcomes will be collected at baseline and 6 and 12 months.

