#### Primary outcome

The primary outcome is functioning of the person with dementia assessed using family carer rated Goal Attainment Scaling (GAS) at 12 months follow-up. GAS is valid, reliable, and responsive to change in function in people with dementia living at home up to 12 months [21, 22]. Trained researchers will work with family carers and people living with dementia to set SMART (Specific, Measurable, Achievable, Realistic and Time-bound) goals across domains including: cognition, instrumental activities of daily life/self-care, mood, behaviour, and mobility. Family carers will evaluate ‘performance’ of the person living with dementia (or carer wellbeing if the goal relates to this) on a minimum of three and maximum of five goals set at baseline, on a 5-point scale ranging from ‘much worse’ to ‘much better’ than expected. As people will have different goals and numbers of goals, a summary formula standardises the degree of goal attainment [21], analysed as a change score. We will calculate GAS for people with dementia who have died, using procedures outlined by Gordon et al. [32]. Where death was unexpected, attainment in each domain will be rated as − 2. Where death was expected (we exclude clients who are considered to be in their last 6 months of life, but circumstances can change and we follow-up clients for 1 year), goals will be rated as achieved prior to death.

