### Sample size {14}

The sample size calculation is based on the primary comparison of Goal Attainment Scaling change scores at 12 months between the intervention and usual care groups. Assuming a moderate effect size of 0.5 [34], 198 intervention and 99 control subjects are required to detect such a difference at a 5% significance level (2-tailed) with 90% power. The calculation includes an inflation for clustering due to therapist in the intervention arm (intracluster correlation coefficient (ICC) = 0.05 average cluster size = 20) and for up to 15% loss to follow-up [35]. The calculation of sample size was carried out using STATA version 14.

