#### Secondary outcome analysis

Analyses of the continuous secondary outcome scores will take a similar approach to the analysis described for the primary outcome; however, models for these outcomes will additionally include adjustment for the associated baseline measurement.

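### The primary outcome is defined and powered as a GAS change score but analysed as a 12-month GAS score with no baseline GAS term

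*Protocol article*

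**What the plan says.** All references are to the protocol article.

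- **Primary outcome:** "a summary formula standardises the degree of goal attainment [21], analysed as a change score".
- **Sample size {14}:** the calculation is "based on the primary comparison of Goal Attainment Scaling change scores at 12 months between the intervention and usual care groups".
- **Primary outcome analysis:** "Family carer-rated Goal Attainment Scaling (GAS) global mean scores at 12 month follow-up will be summarised" by group. That outcome is then compared with a "three level mixed effects model which allows for intervention arm therapist clustering and also includes a random effect for study site". The section goes on: "The treatment effect estimate from this model will be the adjusted difference in mean GAS score". It names neither a change score nor a baseline GAS covariate.
- **Secondary outcome analysis:** the approach is similar to the primary one, but "models for these outcomes will additionally include adjustment for the associated baseline measurement". The word 'additionally' implies that the primary model has no such term.
- **Outcomes {12}:** "All outcomes will be collected at baseline and 6 and 12 months". Table 1 also marks GAS at baseline.

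No section says how a baseline GAS score is obtained, whether it can differ between dyads, or whether the 12-month score is itself what is meant by a change score.

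**The concern.** A confirmatory trial needs one primary variable, because the headline estimate, confidence interval and P value come from it. Here two sections point to 12-month minus baseline, and the section that specifies the model points to the 12-month score alone. If baseline GAS differs between dyads, these are different variables with different variances, and the effect size of 0.5 is attached to one while the model analyses the other.

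This is not detail properly left to the statistical analysis plan. Whichever version that plan adopts, it will depart from part of the protocol. The masking section also says that the statisticians cannot be blinded, so an open choice between two versions invites the criticism that it was made with knowledge of the groups.

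**Working it through.** **Step 1. Reproduce the stated sample size.** Inputs from the Sample size section: effect 0.5, two-sided 5%, 90% power, ICC 0.05, cluster size 20 in the intervention arm only, 15% loss. The 2:1 allocation is from the Trial design section.

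- Design effect, intervention arm: 1 + (20 − 1) × 0.05 = 1.95.
- Control n = (1 + 1.95/2) × (1.960 + 1.282)² / 0.5² = 83.01, rounded up to 84, with 2 × 84 = 168 intervention.
- Loss: 84/0.85 = 98.8, giving 99; 168/0.85 = 197.6, giving 198.

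This matches 198 + 99 = 297. With 15% loss, 168.3 and 84.15 remain, so SE² = 1.95/168.3 + 1/84.15 = 0.02347 and SE = 0.1532 in SD units. Power = Φ(0.5/0.1532 − 1.96) = 90.4%. The calculation uses only a standardised effect. It is valid for either form of the outcome and does not show which was meant.

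**Step 2. When the versions differ.** In simple two-group terms, let D₁ be the difference between groups in mean GAS at 12 months and D₀ the chance difference at baseline.

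- 12-month score: the estimate is D₁.
- Change score: the estimate is D₁ − D₀.

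Under randomisation both target the same effect in raw units, but in a given sample they differ by D₀, and so do their P values. If every dyad has the same baseline score, D₀ = 0. The versions then differ only by a constant, with the same estimate and the same power.

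**Step 3. Illustrative size if baseline GAS varies.** The protocol gives no correlation r between baseline and 12-month GAS, so r is assumed. Equal SDs at both times are assumed, and the clustering is kept as in Step 1. Relative to the 12-month score, the variance is multiplied by 2(1 − r) for change and by 1 − r² for the baseline-adjusted analysis. If 0.5 is in change-score SDs, as the Sample size section suggests:

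- 12-month score without baseline: effect = 0.5 × √(2(1 − r)).
- Baseline-adjusted: effect = 0.5 × √(2(1 − r)) / √(1 − r²).
- Power = Φ(effect/0.1532 − 1.96).

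| r (assumed) | Effect, 12-month score | Power, no baseline term | Power, baseline-adjusted |
|---|---|---|---|
| 0.3 | 0.59 | 97% | 98% |
| 0.5 | 0.50 | 90% | 96.5% |
| 0.6 | 0.45 | 83% | 95% |
| 0.7 | 0.39 | 72% | 94% |
| 0.8 | 0.32 | 54% | 93% |

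**Step 4. Why a baseline covariate removes the conflict.** The model (12-month − baseline) = a + b × arm + c × baseline can be rewritten as 12-month = a + b × arm + (c + 1) × baseline. The treatment coefficient b is the same in both, so with baseline in the model it no longer matters which form is the dependent variable.

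**The case against.** The strongest case for the plan is that GAS is not an ordinary repeated measure. The Primary outcome section says goals are fixed at baseline and later rated against expectation, and the Discussion describes GAS as the degree to which those goals are met. A 12-month attainment score may therefore already express change, and the baseline mark in Table 1 may only record goal setting. On that reading, separating GAS from the secondary scales is deliberate, and a baseline covariate would do nothing. This is plausible and it limits the point. But the article does not say it, and the Outcomes section lists every outcome as collected at baseline.

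The Statistical methods section leaves detail to a separate analysis plan, to be agreed before final data are available. That lowers the risk of a data-driven choice but does not reconcile the conflicting statements.

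A reader might also infer more than the text supports:

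- **That the primary analysis is wholly unadjusted.** It is not: the model includes therapist clustering and site, and the estimate is called adjusted. What is absent is a baseline GAS term.
- **That secondary models adjust for baseline GAS in general.** Each adjusts for its own baseline, which is GAS only for a GAS-type outcome such as the researcher rating.
- **That a summary formula and a global mean score are two rival scorings.** The mean may be taken over formula-derived scores, and the formula lies in a cited source not at hand. No conflict is shown.

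**Conclusion.** The inconsistency stands: change score in the Primary outcome and Sample size sections, 12-month score without baseline GAS in the Primary outcome analysis section. Its consequence depends on one unstated fact, namely whether baseline GAS varies between dyads. If it does, the two versions give different estimates, P values and power. If it does not, the matter is one of wording.

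It is tempting to conclude that the trial is underpowered or its sample size mistaken. The document does not support that. The 198 + 99 reproduces exactly, with 90.4% power after 15% loss. The power of the 12-month analysis lies above or below 90% according to whether r is below or above 0.5, and both r and the equal SDs are assumptions. The table shows how much may hang on the choice; it does not show a loss.

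**What to change.** 1. Name one primary variable, in the same words, in the Primary outcome, Sample size and Primary outcome analysis sections: the 12-month carer-rated GAS summary score.
2. State how baseline GAS is scored and whether it can differ between dyads.
3. State on which scale the 0.5 is expressed: SDs of the 12-month score or of the change score.
4. If baseline GAS varies, add it as a covariate in the primary model, so that change and final score give the same treatment effect. If it is constant, say so and omit the covariate, which could not be estimated separately from the intercept.

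The cost is wording in the protocol and analysis plan and at most one covariate, from an assessment already scheduled at baseline. The sample size need not change.

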The University College London (UCL) and University of Bradford (UoB) employed facilitators have been trained to deliver the NIDUS-family intervention to people living with dementia at home and their family carers. The intervention delivery training is provided by members of the research team (including an old age psychiatrist (CC), clinical psychologists (MP/PR) and the trial manager (AB), and research network volunteers from the Alzheimer’s Society (MO, DS). Initial training took place over 9 days face to face between January and March 2020. Taught content included clinical skills, taught by a clinical psychologist, with most of the time spent role-playing the sessions to practice delivery and troubleshoot scenarios that might arise. Role plays were conducted within the UCL/UoB research teams, and facilitators also role played sessions with PPI representatives with experience of caring, who then gave feedback to the research team. Facilitators were signed off to deliver the first intervention session, subsequent intervention sessions, and the final intervention session using written sign off sheets completed by members of the research team delivering the training. Facilitators attend group supervision with a qualified clinical psychologist every two weeks and can access individual support between formal supervision sessions if needed.

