### Recruitment {15}

Researchers will recruit 297 family carer-people with dementia dyads from memory services or older adult mental health services in NHS Trusts and GP practices supported by the Clinical Research Networks (CRNs): North Thames, Thames Valley and South Midlands, North West London, Kent, Surrey and Sussex, and Yorkshire and Humber. We will aim to recruit 10–20 dyads per trust or GP practice area.

Clinicians and research nurses are asked to contact potential participants during the recruitment period. Verbal permission will be sought from the person living with dementia and the family carer (if present) from the identifying clinician/research nurse, and they will contact the researcher either by telephone or secure email to inform them of any interested participants. The researcher will then contact the person living with dementia and their family carer at least 24 h after the participant information sheet (PIS) has been given by the clinician/research nurse in person, 48 h if it has been sent via email, or at least 72 h if it has been sent by post.

A mail out will also be conducted to all potentially eligible participants at participating GP practices. The mail out will contain the relevant PIS and a letter asking the family carer or person with dementia to indicate their interest in participating in the study either by calling a researcher or returning a reply slip. As researchers receive responses, they will contact the person with dementia and their family carer to answer any questions they may have, check eligibility, determine the context of the situation and relationship, and then, if they would like to, make an appointment to elicit informed consent and conduct the baseline assessment.

The study is also advertised through the social media platform Twitter, the NIDUS study website, and the research organisation Join Dementia Research.

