### Assignment of interventions: masking

#### Who will be blinded {17a}

The researchers collecting outcome data are blinded to group allocations. Four-to-six researchers will work in two small teams, and if a researcher delivers the intervention from one team, a researcher from the other team will conduct the outcome assessments for their participants. Clinical supervision will be conducted with the teams separately to avoid unblinding during discussions. It will not be possible to blind trial participants or researchers delivering the intervention to group allocation, nor will it be possible to blind the statisticians analysing the data due to the 2.1 participant allocation ratio, though analyses will not commence until all data are collected and the database has been locked.

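### Fitted as a dyad–facilitator–site hierarchy, the three-level primary model would split each facilitator across recruiting sites and understate the standard error

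*Protocol article*

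**What the plan says.** The Primary outcome analysis section of the protocol article specifies a "three level mixed effects model which allows for intervention arm therapist clustering and also includes a random effect for study site". It promises an adjusted mean difference with a 95% confidence interval and P value. It does not define site, does not say whether facilitators are nested in or crossed with sites, and names no reference distribution for the test. The Secondary outcome analysis section takes a similar approach to the continuous secondary scores, adding the baseline value. The opening of Statistical methods leaves detail to a separate analysis plan.

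Four other places describe how facilitators relate to sites:
- Intervention description {11a}: "The University College London (UCL) and University of Bradford (UoB) employed facilitators have been trained to deliver the NIDUS-family intervention". The employers are two universities, not the recruiting trusts.
- Study setting {9}: the intervention is delivered by telephone or video call.
- Recruitment {15}: "We will aim to recruit 10–20 dyads per trust or GP practice area".
- Who will be blinded {17a}: "Four-to-six researchers will work in two small teams". A researcher from one team assesses outcomes for dyads treated by the other team, so the same people both deliver and assess.

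The Sample size {14} section uses an "intracluster correlation coefficient (ICC) = 0.05 average cluster size = 20" in the intervention arm.

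**The concern.** Three levels ordinarily means a strict hierarchy in which each therapist belongs to one site. Here a handful of people work remotely for two employers, and dyads come from many more areas than there are facilitators. Each facilitator must therefore serve several areas.

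In software, a hierarchical specification gives a facilitator who works in two sites two separate, independent random effects. The covariance between that facilitator's dyads in different sites is set to zero. Most of the facilitator component then drops out of the variance of the treatment effect, because it is averaged over many small site-by-facilitator cells instead of over four to six people. At stake are the width of the primary confidence interval, the size of the primary test and, through the shared approach, the continuous secondary outcomes.

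**Working it through.** **Inputs from the article.** Effect size 0.5 ("Assuming a moderate effect size of 0.5"), tested "at a 5% significance level (2-tailed) with 90% power"; "198 intervention and 99 control subjects are required to detect such a difference"; ICC 0.05 and mean cluster size 20 in the intervention arm; 15% loss.

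**Inputs assumed.** Site variance 0.02 of the total (0 was also tried); 20 sites unless stated; Wald z test at 1.96.

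**1. The plan's own sample size.** The intervention-arm design effect is 1 + 19 × 0.05 = 1.95. Controls needed: (1 + 1.95/2) × ((1.960 + 1.282)/0.5)² = 1.975 × 42.03 = 83.0. Dividing by 0.85 gives 97.7, so 98 controls and 196 intervention dyads, 294 in all. The stated total is 297, so the calculation reproduces closely. Expected numbers analysed: 198 × 0.85 ≈ 168 and 99 × 0.85 ≈ 84.

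**2. Facilitators and sites.** At 10–20 dyads per area, 297 dyads imply 297/20 ≈ 15 to 297/10 ≈ 30 areas. Four to six facilitators would carry 198/4 ≈ 50 to 198/6 = 33 dyads each. The cluster size of 20 implies 198/20 ≈ 10 facilitators, which does not match four to six researchers. Both counts are carried forward.

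**3. Analytic check.** Site effects roughly cancel because randomisation is stratified by site. With K facilitators and ICC ρ, the true variance of the difference is about ρ/K + (1 − ρ)/168 + (1 − ρ)/84.

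For K = 5 and ρ = 0.05 this is 0.0100 + 0.0057 + 0.0113 = 0.0270, so the SE is 0.164. If the facilitator variance is instead spread over cells of about 2 dyads (168/2 = 84 cells), the first term falls to 0.05/84 = 0.0006 and the SE to 0.133. In simulation the nested fit had a mean SE of 0.134. The effective critical value is 1.96 × 0.134/0.164 = 1.60, which corresponds to a type I error of about 11%.

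**4. Simulation under the null.** 252 dyads analysed, REML fits, 9,000 data sets per scenario (Monte Carlo SE about 0.3 points near 10%), facilitators spread over 20 sites at random:

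| Facilitators | ICC | Nested fit, z | Crossed fit, z |
|---|---|---|---|
| 4 | 0.05 | 13.1% | 7.2% |
| 5 | 0.05 | 11.5% | 6.6% |
| 6 | 0.05 | 10.5% | 6.3% |
| 10 | 0.05 | 7.8% | 5.1% |
| 5 | 0.02 | 7.8% | 5.6% |
| 5 | 0.10 | 17.8% | 7.7% |

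With 5 facilitators and ICC 0.05, the mean SE is 0.134 (nested) and 0.163 (crossed), against an empirical SD of 0.166. A separate simulation of 4,000 trials per setting gave 12.8%, 12.3% and 10.3% for the nested fit with 4, 5 and 6 facilitators.

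**5. Sensitivity to the set-up (ICC 0.05, nested fit, z).**
- 9, 15 or 25 sites, 5 facilitators: 11.0–11.5%.
- Site variance 0, 5 facilitators: 11.5%.
- Facilitators kept within two hubs but spread over each hub's sites: 10.9% (5) and 10.5% (6).
- Each site served by one facilitator: 9.9% (5) and 6.9% (10).
- Site defined as the two hubs: 6.1% (6) and 5.2% (10), identical for both fits.

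**6. Degrees of freedom.** In the separate simulation, the crossed model with Satterthwaite degrees of freedom gave 5.1%, 5.3% and 5.5% with 4, 5 and 6 facilitators. A crude t test on K − 1 degrees of freedom overcorrects: the crossed fit then gives 0.5–1.7% with 4–6 facilitators.

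**The case against.** The strongest reply is that the article never says nested. Its wording also fits two separate random effects with one identifier per facilitator, and the fitted specification is left to an analysis plan that is not shown. A reader might infer that the primary 5% test in this trial simply runs at 10–13%. The article does not support that. The figure needs four things together: hierarchical coding, site meaning recruiting area, four to six facilitators working across areas, and a z test. None is stated outright as part of the primary model. The count of four to six comes from the masking section and concerns researchers. The article's own cluster size points to about 10 facilitators, and no section says how dyads are assigned to them. If site means the two universities, facilitators really are nested and nothing is split.

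A reader might also attribute the whole excess to splitting. That is not so: the crossed model with a z test remains at 6–7% with 4–6 facilitators, so part of it comes from having few clusters.

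All of this stands and makes the size conditional. It does not remove the point. Three level is a stated structure, not an omitted detail, and its ordinary meaning does not fit the delivery that the same article describes.

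**Conclusion.** The concern holds in conditional form. The model as named implies a hierarchy that four to six university-employed facilitators, delivering remotely across about 15–30 recruiting areas, would not satisfy. Fitted literally with site as recruiting area, at ICC 0.05 and with z inference, it gives a type I error of about 10–13% with 4–6 facilitators and about 8% with 10. With 5 facilitators, the range over ICC 0.02 to 0.10 is about 8% to 18%. Under the two-hub reading the error is about 5–6%, and the weakness is instead a random-effect variance estimated from two units. The result rests on the assumed site variance, which made no material difference, and on the assumed spread of facilitators over sites, which moves the 5-facilitator figure between 9.9% and 11.5%. The wording should be settled before the primary analysis, because it governs the main inference.

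**What to change.** Four changes in the analysis plan, and in the protocol wording where it is amended:
1. Define site for the analysis: recruiting trust or practice area, or university hub.
2. Replace three level with a partially clustered, cross-classified model. In the intervention arm, include a facilitator random effect with one identifier per facilitator across all sites. Enter site as a crossed random effect, or as a fixed effect if it means the two hubs.
3. Base the confidence interval and P value on Satterthwaite or Kenward-Roger degrees of freedom, not on a z test.
4. Apply the same structure to the continuous secondary outcomes.

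The change takes a sentence or two and leaves trial conduct alone; it needs the facilitator's identity recorded for each intervention dyad. The price is wider intervals. With 5 facilitators at ICC 0.05, the mean SE rises from 0.134 to 0.163 (0.163/0.134 = 1.22), plus a small further widening from the degrees of freedom. That width reflects uncertainty that is present in the data.

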### Who will take informed consent? {26a}

Trained researchers will assess capacity to consent. They will obtain verbally-recorded or written informed consent (by post after phone or video call discussion; or face to face if COVID-19 restrictions allow) from each family carer and person living with dementia prior to participation, following adequate explanation of the aims, methods, anticipated benefits, and potential hazards and burdens of the trial. Consent will be sought at least 24 h after potential participants have been given the study documentation. The researcher will explain that participants are under no obligation to enter the trial and that they can withdraw at any time during it, without having to give a reason. Family carers of people who lack capacity to consent will be asked to complete a consultee declaration form on behalf of their relative with dementia.

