#### Implementation {16c}

Researchers will enrol participants and collect baseline data. They will enter the data onto the Sealed Envelope database; then, as soon as data entry is complete, they will instigate the randomisation procedure. Sealed envelope provides the allocation on participant registration.

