#### Methods for additional analyses (e.g. subgroup analyses) {20b}

The following supportive analyses will be carried out for the primary and secondary outcomes using the same modelling approaches as described in the ‘Statistical methods’ section of this protocol:

• Adjusted analyses allowing for other predefined factors related to the outcome (whether the family carer participating was living with the care recipient and whether the care recipient had capacity to give informed consent to participate (as an index of dementia severity)).

• Estimation of the treatment effect adjusting for any concerning imbalances in baseline characteristics.

Subgroup analyses will explore the primary outcome in (1) those who receive a minimum ‘dose’ of the intervention, relative to the control group and those who do not, and (2) between participants receiving the intervention predominantly by telephone, video call, and (if applicable) face to face (3).

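### The primary model omits the two dyad-level baseline factors that the protocol predefines as related to outcome: a modest loss of efficiency, not a bias

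*Protocol article*

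**What the plan says.** Under Primary outcome analysis, the protocol article specifies a "three level mixed effects model which allows for intervention arm therapist clustering and also includes a random effect for study site". Besides randomised group, the model therefore holds therapist (intervention arm) and site. Site is the stratification factor, so the model is not free of baseline information, but nothing about the dyad enters it.

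Under Secondary outcome analysis the approach is similar, with one addition: "however, models for these outcomes will additionally include adjustment for the associated baseline measurement".

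Under Methods for additional analyses, the list opens: "The following supportive analyses will be carried out for the primary and secondary outcomes". Its first item is: "Adjusted analyses allowing for other predefined factors related to the outcome". Two factors follow. One is whether the participating carer lives with the care recipient. The other is "whether the care recipient had capacity to give informed consent to participate (as an index of dementia severity").

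On timing, the consent section says: "Trained researchers will assess capacity to consent". The Implementation section says that researchers enter the baseline data and "then, as soon as data entry is complete, they will instigate the randomisation procedure".

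**The concern.** The protocol singles out two baseline characteristics as related to outcome and commits to adjusting for them, yet the headline comparison leaves them out. If they do predict GAS, the variance they explain stays in the error term of the primary model, and the primary interval is wider than it needs to be. Randomisation is stratified by site only, so nothing in the design balances either factor between the arms. Prespecified adjustment for baseline factors would recover that precision without affecting the type I error rate.

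This is not a detail left to the separate statistical analysis plan. The protocol itself has already given these two factors a supportive role, and that choice is what is questioned here.

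**Working it through.** **Inputs.** From the Sample size section: effect size d = 0.5, two-sided 5% level, 90% power, therapist ICC 0.05 in the intervention arm, average cluster size 20, 15% loss, and 198 + 99 dyads. R², the share of dyad-level outcome variance explained by the two factors, is not in the documents. It is assumed at 0.02, 0.05 and 0.10.

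**Step 1: reproduce the plan's figure.**
- Design effect in the intervention arm: 1 + 19 × 0.05 = 1.95.
- Controls needed at 2:1: ((1.960 + 1.282)/0.5)² × (1 + 1.95/2) = 42.03 × 1.975 = 83.01, rounded up to 84, with 168 in the intervention arm.
- After 15% loss: 84/0.85 = 98.8, rounded up to 99; 168/0.85 = 197.6, rounded up to 198.

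This matches the stated 198 and 99 exactly, with no allowance for covariates. The planned power therefore does not depend on adjustment.

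**Step 2: standard error with and without the factors.** With 168 and 84 analysed there are 168/20 = 8.4 therapist clusters. Covariates are taken to reduce dyad-level variance only:

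SE = √[0.05/8.4 + 0.95(1 − R²)/168 + (1 − R²)/84]

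Power = Φ(0.5/SE − 1.96)

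At R² = 0 the three terms are 0.00595 + 0.00565 + 0.01190 = 0.02351, so SE = 0.1533 and power = Φ(1.30) = 90.3%.

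| R² (assumed) | SE | Power | 95% CI half-width (SD) | CI narrower by |
|---|---|---|---|---|
| 0 | 0.1533 | 90.3% | 0.300 | – |
| 0.02 | 0.1522 | 90.7% | 0.298 | 0.8% |
| 0.05 | 0.1504 | 91.4% | 0.295 | 1.9% |
| 0.10 | 0.1475 | 92.4% | 0.289 | 3.8% |

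**Step 3: the same gain in dyads.** The variance ratio is 0.02263/0.02351 = 0.963 at R² = 0.05 and 0.02176/0.02351 = 0.925 at R² = 0.10. Their reciprocals are about 1.04 and 1.08, so the gain equals about 12 and 24 further dyads on 297, with therapists added in proportion.

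**Step 4: a more favourable case.** If the factors also reduced the between-therapist variance in proportion, power at the three values of R² would be 90.9%, 91.8% and 93.1%, and the interval would be 1.0%, 2.5% and 5.1% narrower. (This case uses unrounded analysed numbers, 84.15 and 168.3, with baseline power 90.4%.) The conclusion is the same.

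**Step 5: are the factors available?** Capacity is assessed at consent, so it is known before allocation. For co-residence no section says outright that it is recorded for every dyad before randomisation. It is a reasonable inference, because Table 1 schedules demographics at baseline and the adjusted analysis already requires it.

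**The case against.** The strongest reply is that nothing here is wrong. A simple prespecified primary model with a prespecified adjusted analysis beside it is a legitimate choice. It includes the stratification factor, models therapist clustering, follows intention to treat and reaches its 90% power. The adjusted estimate will be reported anyway, so the proposal only exchanges two labels. All of this stands, and it limits the point to efficiency.

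It also stands that the gain could be close to nil. The description of the factors as related to outcome covers primary and secondary outcomes together and gives no strength of association with GAS. Because goals are set individually to be achievable and realistic, severity and living situation may be partly absorbed when they are set.

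A reader might infer more than the documents support:
- **That the primary result is biased or underpowered.** It is neither. The interval of a valid unadjusted test already allows for chance imbalance, and 2:1 allocation does not change that.
- **That two estimates falling on different sides of 5% is a defect.** The plan says which analysis is primary, and a second estimate would still exist after the swap.
- **That baseline GAS should be in the model, as the secondary outcomes have their baseline values.** The primary outcome is analysed as a change score on goals set at baseline, so the contrast with the secondary models does not show an omission.

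What the reply does not answer is why factors that the trial has itself selected, defined and committed to using should be kept out of the analysis that decides the result, when including them costs almost nothing.

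**Conclusion.** The point holds as a modest and avoidable loss of efficiency. On the assumed R² of 0.02 to 0.10, the primary analysis gives up about 0.4 to 2.1 percentage points of power (90.7 − 90.3 and 92.4 − 90.3), and its interval is roughly 1% to 4% wider than it need be. The direction is certain only if R² exceeds zero, and the size rests wholly on that assumption. If the factors are unrelated to GAS, adjustment costs two degrees of freedom out of about 252 analysed dyads. The trial's conclusions would be valid without the change.

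**What to change.** In Primary outcome analysis, state that the fixed effects are randomised group, whether the carer lives with the care recipient (yes/no) and whether the care recipient has capacity to consent (yes/no), alongside the therapist and site terms already given. Both factors should take their baseline values, including where a second carer later replaces the first. Name capacity to consent itself rather than dementia severity, since it is the defined variable and Table 1 lists no separate severity measure. Confirm that co-residence is captured on the baseline form for every dyad.

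In Methods for additional analyses, replace the adjusted analysis of the primary outcome with the model without these two factors, as the supportive analysis. Because the secondary outcome models follow the primary approach, say whether the two factors carry over to them.

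Settle this in the protocol and the analysis plan before outcome data are released. The cost is wording and two degrees of freedom. It requires no change to the sample size and, once co-residence is confirmed as recorded, no new data.
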